## Abstract

**Introduction:**

The incidence of metastatic prostate cancer (mPCa) is increasing despite a decrease in the prevalence of prostate cancer (PCa). Androgen deprivation therapy (ADT), the mainstay of systemic treatment for mPCa, is associated with numerous side effects, including a decline in muscle mass and physical function, which lead to the exacerbation of age-related frailty and sarcopenia. Exercise plays a key role in ameliorating or preventing the progression of ADT-related side effects and in improving muscle mass, fitness, and strength. However, exercise interventions in patients with mPCa have been understudied, with a lack of studies focusing on frailty and sarcopenia and the mechanisms by which exercise could address these issues.

**Purpose:**

Thus, we have designed the FIERCE trial to assess the effects of a 16-week multicomponent exercise intervention, encompassing resistance and aerobic training, on frailty and sarcopenic status and their potential mechanistic biomarkers, as well as on cancer cell proliferation (NCT06040125).

**Methods:**

The FIERCE trial is a prospective study aiming to recruit 80 pre-frail/frail men with mPCa receiving ADT who will be randomized to either an exercise or an attention control group. The 16-week exercise intervention will include thrice-weekly, clinic-supervised, resistance exercise circuit training and self-directed home-based aerobic exercise. The attention control group will receive a stretching program and will be offered the exercise program following the study period. The primary outcome is frailty, measured by the Fried frailty phenotype (i.e., muscle loss, exhaustion, physical activity, gait speed, and strength) and frailty-associated biomarkers [IL-6, TNF-α, C-reactive protein (CRP)]. Secondary outcomes include sarcopenia, measured using dual-energy x-ray absorptiometry scans and sarcopenia-associated muscle biopsy-driven biomarkers (myokines and insulin pathway markers). An exploratory outcome will assess how exercising patient-derived plasma will affect the proliferation of prostate cancer cells (LNCaP cells).

**Conclusion:**

This first-of-its-kind study targets a vulnerable, understudied population: frail men with mPCa. If successful, our findings will establish the efficacy of a multicomponent exercise intervention on frailty and sarcopenic status, providing the foundation for future larger phase II and III trials to confirm the findings and potentially establish exercise as a safe and necessary part of the standard of care for frail metastatic prostate cancer patients.

## Introduction

1

Androgen deprivation therapy (ADT), the mainstay systemic treatment for men with recurrent and/or metastatic prostate cancer (mPCa), works by depriving the body of hormones such as testosterone. Given the critical role testosterone plays in activating lipolysis and promoting lean mass hypertrophy, substantial body composition changes and loss of muscle strength and physical function can occur leading to the development or exacerbation of geriatric syndromes such as frailty and sarcopenia (1). Frailty, a comprehensive loss of functional reserve in multiple physiological systems, is a common clinical concern found in 40%–90% of men with PCa on ADT and is associated with a worse prognosis (2–5). Specifically, severely frail men showed an 86% higher risk of all-cause mortality and a 44% increased risk of cancer-specific mortality compared with their non-frail counterparts (4). Similarly, sarcopenia, characterized by a decrease in muscle mass, strength, and function, occurs in >80% of men with mPCa on ADT (6–8) and is an independent risk factor of cancer-specific mortality (9). An intervention that can address frailty and sarcopenia, alongside persisting ADT-related concerns, is critical to improve the clinical care of this population.

Aerobic and resistance training is a recommended complementary therapy for PCa patients and has been shown to prevent further deterioration of ADT-related adverse effects, such as skeletal muscle mass loss, fat mass gain, and reduced cardiorespiratory fitness and muscular strength (10–13). In addition, the inclusion of functional movements (e.g., balance) can maximize the beneficial effects of exercise on physical function, muscular strength, muscular endurance, and body composition (14–19). Within the context of frailty and sarcopenia, a multicomponent exercise intervention is recommended, given the multifaceted exercise stimulus that is required of an intervention to target the various characteristics of both syndromes (20). Nevertheless, men with mPCa are largely underrepresented in previous exercise oncology research, and no studies have specifically focused on frailty and sarcopenia in this population (20–23). Thus, a rigorously designed randomized controlled trial is warranted, which examines an exercise prescription specifically targeting the frailty–sarcopenia–ADT axis in frail men with mPCa.

Understanding whether exercise prevents or reverses frailty and sarcopenia, as well as the mechanisms implicated, is critical for improving health and quality of life in men with mPCa on ADT, yet the mechanisms by which exercise improves frailty and sarcopenia, particularly in the context of ADT, are unknown (7). Proposed mechanisms are improvements in systemic inflammatory and skeletal muscle tissue-related outcomes (7). Thus, we will investigate systemic inflammatory biomarkers associated with frailty [IL-6, TNF-α, C-reactive protein (CRP)] and muscle tissue-related outcomes associated with sarcopenia (myokine release and activation of insulin pathway-related biomarkers) to aid in refining explanations surrounding the frailty–sarcopenia–ADT axis with exercise (5, 24–29). In addition, exploring whether the effects of exercise are associated with biochemical cancer progression will provide insight into understanding the roles of exercise in long-term oncologic outcomes in the context of mPCa.

The overall objective of the FIERCE trial is to evaluate the efficacy of a 16-week multicomponent exercise intervention encompassing supervised, clinic-based circuit training utilizing resistance exercises and self-directed aerobic exercise on frailty and sarcopenia with an exploration of novel biomarkers at the intersection of frailty, sarcopenia, and disease progression. The primary outcome of this study is change in frailty score, measured by the Fried frailty phenotype (i.e., muscle loss, exhaustion, physical activity, gait speed, and strength) and frailty-associated biomarkers (IL-6, TNF-α, CRP). Secondary outcomes include change in sarcopenia status, measured using a computerized tomography (CT) scan and sarcopenia-associated muscle biopsy-driven biomarkers (myokines and insulin pathway markers). An exploratory outcome will assess how plasma from patients undergoing the exercise intervention affects prostate cancer cell proliferation (LNCaP cells). We hypothesize that the exercise group, compared with the attention control group, will exhibit the following: (1) a lower proportion of frail and pre-frail scores and improved individual scores of each frailty component; (2) improvements in systemic inflammatory biomarkers; (3) improved sarcopenia status; (4) increased gene and protein expression of muscle biopsy-driven anti-inflammatory myokines and insulin pathways; and (5) suppressed biochemical progression of PCa.

## Methods

2

### Study design

2.1

The FIERCE trial is a two-arm randomized controlled trial underway at the Dana-Farber Cancer Institute (NCT06040125). Outcomes are measured at baseline (week 1) and at post-intervention (week 18). A total of 80 men diagnosed with metastatic prostate cancer, who have a history of or are currently receiving, androgen deprivation therapy and are considered pre-frail or frail, are randomized to one of two groups: (1) intervention group, who will receive a 16-week supervised, clinic-based, multicomponent exercise intervention in conjunction with self-directed aerobic exercise or (2) attention control group, who will receive a home-based stretching program. Those randomized to the attention control group will be offered the exercise program following the initial 16-week study period (Figure 1).

**Figure 1 F1:**
[figure not shown]
Study schema for the FIERCE trial.

### Participant eligibility

2.2

Men are eligible if they meet the following criteria: (1) diagnosed with metastatic prostate cancer; (2) aged >18 years; (3) have received at least 3 months of androgen deprivation therapy or are currently receiving at least 1 month of androgen deprivation therapy and are expected to remain on therapy for the duration of the study; (4) classified as pre-frail or frail as determined by the FRAIL scale (score of 1–2 = pre-frail; 3–5 = frail) (30–33); (5) medically cleared by their clinicians for exercise; (6) English-speaking; and (7) inactive (defined as engaging <60 min of moderate-to-vigorous aerobic exercise per week in the past month or <2 resistance exercise sessions per week in the past 4 months). Exclusion criteria include the following: (1) actively receiving chemotherapy or radiotherapy; (2) having unstable bone lesions; (3) having any uncontrolled comorbidity, condition, or contraindication that may prevent participation in exercise; and (4) receiving treatment for other active malignancy (except basal cell carcinoma).

### Recruitment and informed consent

2.3

Participants are currently being recruited through clinician referral and screening of participant lists at the Dana-Farber Cancer Institute, Boston, MA, USA, as well as by way of advertisements in participant waiting rooms, the Partners Rally Platform, and other relevant prostate cancer community groups and events. All participants require clinician clearance before being formally screened via phone. Phone screening comprises three short questionnaires to determine eligibility: the Godin Leisure Time Questionnaire (34) to assist in determining current exercise levels, the Physical Activity Readiness Questionnaire (35) to confirm health status and how this relates to undertaking an exercise program, and the FRAIL questionnaire (30–33) to assess frailty status. Upon confirmation of eligibility and interest, participants consent via wet or electronic signature.

### Ethics approval

2.4

The study has been approved by the Institutional Review Board at the Dana-Farber Cancer Institute (IRB #23-109). The studies were conducted in accordance with the local legislation and institutional requirements. The participants provided their written informed consent to participate in this study.

### Measurements

2.6

#### Overview

2.6.1

Testing is completed over 2 days at baseline and post-intervention. Order of days is divided by a collection of biospecimens (i.e., blood and muscle tissue) and non-physical tests (i.e., questionnaires and body composition) completed on 1 day, and all other physically demanding tests are completed on the other (∼2–3 days apart). This separation of measures is to ensure participants can recover from the biopsy and not complete any physically demanding activities that may influence blood or muscle biomarkers. All measures are collected at all time points by study staff members trained in exercise oncology unless otherwise specified (Table 1).

**Table 1 T1:** Outcome measures by study visits for the FIERCE trial.

Timepoint	Week 0	Week 1–17	Week 18	Week 19–34^a^
Enrollment				
Eligibility screen	X			
Phone screen	X			
Informed consent	X			
Randomization	X			
Interventions				
Circuit training + self-directed aerobic exercise		X		X (optional)
Attention control		X		
Assessments				
Fried frailty phenotype measures	X		X	
Muscle biopsy (optional)	X		X	
Blood biomarkers	X		X	
Anthropometrics	X		X	
Patient-reported outcomes	X		X	
Cardiorespiratory fitness	X		X	
Physical function	X		X	
Strength	X		X	
Physical activity	X	X	X	
Diet	X		X	
Exit survey			X	

^a^
Applies to the attention control group and is optional.

#### Primary outcomes

2.6.2

##### Fried frailty phenotype

2.6.2.1

The Fried frailty phenotype is a composite score of the five measures: muscle loss, exhaustion, physical activity, slowness, and weakness. Participants receive a score of 1 (experience muscle loss, exhaustion, etc.) or 0 (do not experience) for each characteristic, with a total score of 1–2 identified as pre-frail and ≥3 as frail (36, 37). The Fried frailty phenotype was selected as it offers the most accurate way to capture frailty status using objective measures with pre-determined cutoff points (1, 36). A modified version of the Fried frailty phenotype was selected to tailor to the known effects of ADT, e.g., muscle loss, to ensure frailty was captured in a way that was tailored to the studied population, as has been proposed by other prostate cancer studies assessing frailty (1, 36).

###### Muscle loss

2.6.2.1.1

A skeletal muscle index (SMI—calculated as appendicular skeletal muscle mass / height^2^) sarcopenia score of ≤7.26 kg/m^2^, as assessed by dual-energy x-ray absorptiometry (DXA) scan, is the cut point used for identifying muscle loss = 1 point (6, 38). In addition, in a subset of patients with available standard of care computed tomography (CT) scans within ∼1 month of baseline and post-intervention time points, sarcopenia will also be assessed with a skeletal muscle index of ≤52.4 cm^2^/m^2^ as the cut point used for identifying muscle loss = 1 point (39). Skeletal muscle area is measured on axial CT images at the level of the L3 vertebral body using a validated, fully automated algorithm (40). SMI is calculated as the ratio of muscle area (cm^2^) to squared height (m^2^). A CT series will be analyzed into two steps: (1) a convolutional neural network model is used to identify a slice at the L3 level, and (2) the chosen slice is passed to a segmentation model to estimate the cross-sectional areas of muscle (40).

###### Exhaustion

2.6.2.1.2

Exhaustion is assessed using the vitality score from the Short Form Health Survey (SF-36), a 36-item questionnaire assessing quality of life. A cut point of <50 for those 50–65 years and <40 for those >65 years is used to identify exhaustion = 1 point (36, 37, 41).

###### Low physical activity

2.6.2.1.3

The Community Health Activities Model Program for Seniors’ physical activity questionnaire is used to assess physical activity, with low activity defined as <383 kcals = 1 point (36, 37). This is a 41-item questionnaire asking about time spent undertaking certain physical activities (42).

###### Slowness

2.6.2.1.4

Usual gait speed is assessed over a 15-foot flat surface distance with an average time over two attempts of ≥7 s for participants ≥173 cm tall or ≥6 s for those <173 cm tall considered as “slow” = 1 point (36, 37). In addition, the participant is asked to walk at their “fast” pace for the 15-foot distance a further two times, but this is not utilized for the Fried frailty phenotype composite score.

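### The slowness limits in the primary frailty score give taller men more time than shorter men, the reverse of a height adjustment; they appear transposed and should be verified before scoring

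*Protocol article*

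**What the plan says.** Section 2.6.2.1.4 of the protocol article defines the test: "Usual gait speed is assessed over a 15-foot flat surface distance". The item scores one point at an "average time over two attempts of ≥7 s for participants ≥173 cm tall or ≥6 s for those <173 cm tall". The limits are attributed to references 36 and 37.

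Section 2.6.2.1 says the phenotype was chosen because it captures frailty "using objective measures with pre-determined cutoff points". It adds: "A modified version of the Fried frailty phenotype was selected to tailor to the known effects of ADT, e.g., muscle loss". Each of the five items scores 0 or 1, "with a total score of 1–2 identified as pre-frail and ≥3 as frail".

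Section 2.12 makes the 0–5 total the primary outcome, compared by the Wilcoxon rank-sum test. It also plans Fisher's exact test and an odds ratio for each of the five criteria, for hypothesis generation. The gait limits are stated nowhere else in the article.

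**The concern.** A height split in a timed walk over a fixed distance allows for stride length. A taller man covers 15 feet sooner at the same level of function, so the taller group should have the shorter limit. The printed rule does the opposite and therefore enlarges the height effect that the split should remove. This follows from the purpose of the split and needs no outside source.

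The item supplies one of the five points in the primary outcome. One point can carry a man across the 0/1 boundary (not frail to pre-frail) or the 2/3 boundary (pre-frail to frail). The first matters most here: Table 4 anticipates 15% of control men and 85% of intervention men at score 0, so much of the anticipated contrast lies there.

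**Working it through.** The article gives no figure to reproduce for this item. The check applies the rule as printed and then with the height groups exchanged.

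**Inputs (2.6.2.1.4).** Distance 15 ft = 15 × 0.3048 m = 4.572 m. Limits: 7 s at 173 cm or taller, 6 s below 173 cm.

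**Speeds at the limits.**
- 173 cm or taller: 4.572 / 7 = 0.653 m/s.
- Below 173 cm: 4.572 / 6 = 0.762 m/s.
- Ratio: 7 / 6 = 1.167. As printed, the shorter man must walk about 17% faster than the taller man to avoid the point.

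**Item score under each rule.**

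| Time | Height | As printed | Groups exchanged |
|---|---|---|---|
| 5.9 s | 165 cm | 0 | 0 |
| 5.9 s | 185 cm | 0 | 0 |
| 6.5 s | 165 cm | 1 | 0 |
| 6.5 s | 185 cm | 0 | 1 |
| 7.0 s | 165 cm | 1 | 1 |
| 7.0 s | 185 cm | 1 | 1 |

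Every man from 6 s up to, but not including, 7 s changes by one point, and nobody else changes. Taller men go from 0 to 1 and shorter men from 1 to 0. The changes run in opposite directions, so the overall proportion slow could look unremarkable while individual scores are wrong.

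**Share of men in the 6 to under 7 s band.** The article gives no gait distribution, so these are assumptions.

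| Assumed distribution | Share in band | Of 72 |
|---|---|---|
| Speed, mean 0.8 m/s, SD 0.15 | 23.6% | 17.0 |
| Speed, mean 0.9 m/s, SD 0.20 | 13.7% | 9.8 |
| Speed, mean 1.0 m/s, SD 0.20 | 7.6% | 5.4 |
| Speed, mean 1.1 m/s, SD 0.15 | 1.1% | 0.8 |
| Time, mean 5.0 s, SD 1.2 s | 15% | 11 |
| Time, mean 5.5 s, SD 1.2 s | 23% | 17 |
| Time, mean 6.0 s, SD 1.5 s | 25% | 18 |

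All distributions are normal. Across them the share is about 1% to 25%, or roughly 1 to 18 of the 72 men in the planned analysis population (2.11).

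**Plausibility of the upper end.** The anticipated mean totals in Table 4 are 0.63 + 2 × 0.17 + 3 × 0.04 + 4 × 0.01 = 1.13 for control and 0.14 + 2 × 0.01 = 0.16 for intervention. Suppose heights split evenly at 173 cm (an assumption). Times with mean 5.5 s and SD 1.2 s give, as printed, (33.9% + 10.6%) / 2 = 22% slow. That one item would add 0.22 points, more than the 0.16 anticipated for all five in the intervention arm. The upper end of the range therefore cannot describe that arm at week 18 as Table 4 foresees it.

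**Effect on responsiveness.** Take a man who improves from 6.8 s to 5.5 s. If tall, he scores 0 and 0 as printed but 1 and 0 with the groups exchanged, so his gain is missed. If short, he scores 1 and 0 as printed but 0 and 0 exchanged. The net effect on the contrast depends on the mix of heights and times, which the article does not give.

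**The case against.** The strongest reply is that transposition cannot be proved from this document. References 36 and 37 are not shown and the limits appear only once, so no second statement contradicts them. The slip may lie in the article alone, with the full protocol and scoring program correct. This stands, and it is why the first step is a check. It does not defend the printed direction, for which the article offers no reason.

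Several stronger readings are tempting and are not supported:

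- **That the trial's frailty rates are not comparable with the cited phenotype.** This needs the cut-points in the cited sources, which the document does not reproduce.
- **That the stated modification was confined to muscle loss, so the gait limits must be unaltered.** Section 2.6.2.1 offers muscle loss only as an example. The fair statement is that no change to the gait limits is described or explained.
- **That 15–25% of men are affected.** Those shares come only from assumed mean times of 5.0–6.0 s, close to the limits. Faster assumed walking speeds bring the share down to about 1%.
- **That the comparison between arms is biased or its power demonstrably reduced.** The same rule applies to both randomized arms, so neither is favoured. No calculation establishes a loss of contrast, and the examples above show that single cases can go either way.

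Eligibility (2.2) and stratification (2.5) use the FRAIL scale, so neither is touched.

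**Conclusion.** The point holds as a scoring rule that is wrong as written: the height adjustment runs backwards, without explanation, in a component of the primary outcome. If the rule is applied as printed, each man timed at 6 s to under 7 s gets the wrong slowness point, 0 instead of 1 if tall and 1 instead of 0 if short. His primary score shifts by one, and the separate slowness analysis is affected too.

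The number of men is unknown. The range of about 1–25% (1–18 of 72) rests entirely on assumed gait distributions. The consequence is misclassification that favours neither arm, with a possible loss of sensitivity of unknown size. Whether the fault is in the article's text or in the rule actually in use cannot be settled from the document.

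**What to change.** Before any analysis, compare the two limits with references 36 and 37, the full protocol and the scoring program.

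- If the limits are transposed in the rule in use, exchange the height groups in 2.6.2.1.4 and in the scoring code. Then rescore the slowness item and the total at baseline and week 18 from the recorded times and heights.
- If the scoring program is right and only the article is wrong, correct the article's text.
- If the printed direction is intended, state the reason in 2.6.2.1.4.

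The cost is one line of text and at most one rerun of the scoring. Walk times and height are already needed to score the item, and height also enters the skeletal muscle index (2.6.2.1.1), so no new data are required. The individual walk times should be kept as well as the 0/1 item so that rescoring remains possible.

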###### Weakness

2.6.2.1.5

The chair stand test is used to assess leg strength, where a time ≥12 s to complete five chair stands is considered weaker = 1 point (36, 37). Participants are asked to sit in a chair with their hands crossed over their chest. While keeping the feet flat and back straight, participants rise to a full standing position and then sit back down, repeating five stands as fast as they can.

##### Blood biomarkers

2.6.2.2

A trained phlebotomist performs a fasting blood draw, obtaining both serum-separating tubes and ethylenediaminetetraacetic acid (EDTA) samples. After being processed and aliquoted, the blood serum and plasma samples are stored in a −80°C freezer for later batched analysis. Analysis of blood through commercially available kits (Thermo Fisher Scientific) will be used for biomarkers relating to inflammation, frailty, or sarcopenia (i.e., IL-6, TNF-α). Plasma will also be used for exploratory studies assessing effects on prostate cancer cell proliferation.

#### Secondary outcomes

2.6.3

##### Sarcopenia status

2.6.3.1

As described under assessing muscle loss as part of the Fried frailty phenotype.

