### Statistical analysis

2.12

This study will assess whether a 16-week, multicomponent exercise intervention will improve the frailty status of mPCa on ADT. Furthermore, we will assess the effect of the intervention on sarcopenia status, skeletal muscle-derived biomarkers, and cell proliferation rate.

A total of 80 eligible patients who complete the baseline assessment will be randomly assigned to the exercise or attention control groups in an allocation ratio of 1:1 using a permuted blocked design with varying block size (with investigators blinded to block size). The randomization will be stratified by frailty status (pre-frail vs. frail) at baseline assessment.

All analyses will be performed based on the intention-to-treat principle. We will repeat the same analyses with the subjects who complied with the protocol as secondary analyses. Baseline demographic and clinical measures, as well as baseline values of trial outcomes, will be presented by randomized intervention group; continuous measures will be summarized by mean (SD) or median (IQR) and categorical measures by frequencies (percent's). The randomized groups will be compared concerning baseline demographic and clinical variables using two-sample *t*-tests, Wilcoxon rank-sum tests, or Fisher's exact tests to confirm baseline comparability. These variables will be included in the adjusted analyses if clinically meaningful or statistically significant differences are identified.

The primary outcome is the score based on the Fried frailty phenotype (37), which consists of five criteria, and the score will take an integer value from 0 to 5. The Wilcoxon rank-sum test will be used as the primary analysis for comparing the score distribution between groups. Mean score and a corresponding 0.95 confidence interval (CI) will be calculated. We will also assess the intervention effect on each of the five criteria for the frailty phenotype for hypothesis generation purposes. For each, we will perform Fisher's exact test for the between-group comparison and estimate an odds ratio and a corresponding 0.95 CI. Regression analysis will be used to identify baseline factors associated with the outcomes, where proportional odds models will be used for the score as an ordered categorical variable with six categories, and logistic regression models will be used for each of the five criteria.

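### In the full sample, secondary sarcopenia status is the same DXA yes/no item that counts in the primary frailty score; continuous, baseline-adjusted muscle index should be named as its main analysis

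*Protocol article*

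**What the plan says.** - Section 2.6.3.1 (Sarcopenia status) consists of one cross-reference: "As described under assessing muscle loss as part of the Fried frailty phenotype".
- Section 2.6.2.1.1 (Muscle loss) makes the referenced item binary. An appendicular SMI of 7.26 kg/m² or less, "as assessed by dual-energy x-ray absorptiometry (DXA) scan, is the cut point used for identifying muscle loss = 1 point". A second binary cut on the L3 index, 52.4 cm²/m², applies "in a subset of patients with available standard of care computed tomography (CT) scans within" about a month of each time point.
- Section 2.6.2.1 counts muscle loss as one of five 0/1 items in the primary 0–5 score. Table 1 schedules these measures at week 0 and week 18.
- Section 2.12 (Statistical analysis) compares each of the five criteria by Fisher's exact test for hypothesis generation, "for the between-group comparison and estimate an odds ratio and a corresponding 0.95 CI". Other continuous outcomes get a two-sample t-test. Longitudinal data get mixed models, with a logit link if binary. None of these rules mentions sarcopenia status or SMI by name.
- The abstract and the Introduction name different scans. Abstract: "Secondary outcomes include sarcopenia, measured using dual-energy x-ray absorptiometry scans". Introduction: "Secondary outcomes include change in sarcopenia status, measured using a computerized tomography (CT) scan". The Introduction also makes improved sarcopenia status the third of five hypotheses.

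**The concern.** Sarcopenia stands beside frailty in the trial's stated purpose, so a reader will expect the sarcopenia result to be a second line of evidence. In the full sample it is one fifth of the primary score reported again. The same DXA comparison thus has two roles: a hypothesis-generating component analysis in section 2.12, and the test of a stated hypothesis in the Introduction.

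The outcome as defined also reduces a measured quantity to yes or no. A man whose muscle index rises but stays on the same side of 7.26 kg/m² contributes nothing to the comparison. If exercise produces a moderate gain in muscle, the stated endpoint could easily miss it, and a null result on this aim would say little.

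**Working it through.** **Inputs from the protocol article.** Section 2.11: 72 analysed (80 less 10%), two-sided alpha 0.05, d = 0.67 for continuous outcomes, h = 0.415 for binary criteria. Section 2.12: 1:1 allocation. I take 36 per arm, which assumes equal attrition.

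**1. The plan's own figures.**
- Continuous: noncentrality = d·√(n/2) = 0.67 × √18 = 2.84 on 70 df, giving power 80.05%. The stated 80% reproduces.
- Binary: power = Φ(h·√(n/2) − 1.96) = Φ(0.415 × 4.243 − 1.96) = Φ(−0.20) = 42%. The stated 80% does not reproduce for 36 per arm, two-sided; 80% needs h = 0.66. This is a separate matter, but the stated figure cannot be used to show that the binary item is adequately powered.

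**2. Cost of the cut point alone.** Assume SMI is normal, a proportion p0 of controls lies at or below the cut, and the intervention shifts SMI up by d standard deviations. Then p1 = Φ(z(p0) − d). For example, at d = 0.67, p0 = 50% gives p1 = 25.1%, and p0 = 80% gives p1 = 56.8%. Exact Fisher power with 36 per arm:

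| d | t-test on SMI | Fisher on cut point, p0 from 20% to 80% |
|---|---|---|
| 0.67 | 80% | 26–50% |
| 0.50 | 55% | 17–28% |
| 0.30 | 24% | 8–11% |

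The document's only prevalence figure is above 80% (Introduction). At p0 = 80% and d = 0.67, Fisher has about 47%.

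**3. The same in kg/m², adding baseline.** Assumed, not in the document: SD 0.9, true gain 0.3, baseline to week-18 correlation ρ of 0.7–0.9.
- t-test on week-18 SMI: d = 0.3/0.9 = 0.33; noncentrality 0.333 × √18 = 1.41; power about 29% (28–29% by simulation).
- Fisher on the cut point: with a control mean of 7.26, p0 = 50% and p1 = Φ(−0.333) = 36.9%, power 13%. With a control mean of 6.5, p0 = 80.1% and p1 = 69.5%, power 12%. Simulation gives 11–14%.
- SMI adjusted for baseline: residual SD = 0.9 × √(1 − ρ²).

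| ρ | residual SD | 0.3 / residual SD | power |
|---|---|---|---|
| 0.7 | 0.643 | 0.467 | about 50% |
| 0.8 | 0.540 | 0.556 | about 64% |
| 0.9 | 0.392 | 0.765 | about 89% |

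Simulation gives 48–90% over this range.

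The two steps should be kept apart. Dropping the cut point takes power from 11–14% to 28–29%. The further rise to 48–90% comes from the baseline adjustment and depends on the assumed correlation.

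**The case against.** **Section 2.12 does not assign Fisher's test to this secondary outcome.** This stands. The test is assigned to the five criteria and reaches sarcopenia status only by inference. A logit mixed model using both visits is another possible reading. The Fisher figures show what the cut point costs under the one test that is explicitly attached to the item.

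**A reader might infer that the plan discards the continuous DXA value.** The document does not say so. SMI is calculated, and the generic t-test rule could cover it. What can be said is that continuous SMI is not named as an outcome, and that the t-test rule does not use baseline.

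**A reader might infer that the secondary outcome adds no evidence at all.** That goes too far. Reporting a component on its own shows whether muscle drives the composite, and the CT subset is a second measurement. Overlap with a composite is also a legitimate choice if it is acknowledged.

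**If the Introduction governs, the outcome is CT-based and not the same variable.** This is a fair point and shows that the text needs reconciling. It does not rescue the full-sample outcome, because section 2.6.2.1.1 has CT available only for some patients.

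**The kg/m² figures rest on outside assumptions, and the proposed analysis may itself be underpowered.** Both are true. At a correlation of 0.7 it has only about 48–50% power for a gain of 0.3 kg/m². The comparison at d = 0.67 does not use those values.

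**A yes/no status matches the third hypothesis as worded.** This stands, and is the reason to keep the status as a supportive result.

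**Conclusion.** The point holds in this form. For the full sample, sarcopenia status is the DXA yes/no item already counted in the primary score. It is therefore not independent of the primary outcome, and it repeats a comparison that the plan calls hypothesis-generating. Continuous DXA SMI is not named as an outcome, although the data will exist at both visits.

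At the protocol's own d = 0.67, using the cut point lowers power from 80% to about 26–50%. That range rests on normality, 36 per arm and an assumed control prevalence of 20–80%. The loss also appears near the only prevalence the document gives. The larger gap, 11–14% against 48–90%, needs the assumed SD, gain and correlation, and much of it comes from baseline adjustment.

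This weakens a secondary aim. It does not affect the primary Wilcoxon comparison. The change is worth making because it is cheap and recruitment is still under way, so it can be prespecified.

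**What to change.** 1. Name continuous DXA SMI at week 18 as the main analysis of the secondary sarcopenia outcome. Compare arms by linear regression adjusted for baseline SMI and the FRAIL stratum used in randomisation.
2. Keep the proportion at or below 7.26 kg/m² as a supportive result, and state that it is the muscle-loss criterion of the primary score.
3. Reconcile the abstract (DXA) with the Introduction (CT), and report the CT index as a subset analysis because scans exist only for some patients.

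The cost is wording only: section 2.6.3.1, one sentence in section 2.12, and the outcome statement in the Introduction. No new measurement is needed. The small downside is that the main sarcopenia result becomes a difference in kg/m² rather than a status.
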